### Data Analysis

The training data will be used to further develop the signal extraction and processing methodology. The test data will subsequently be used to determine the performance of Lifelight against the targets set out in Table 2.

All statistical analyses will be performed using Microsoft Excel. All analyses will be completed per protocol since there is no intention to treat.

There will be no imputation of missing or implausible data, and any missing, implausible, or problematic readings will be excluded from the analysis. If the Lifelight software is unable to detect the participant’s face during the measurement period, this will be recorded in the electronic case report form, and the measurements will be deleted from the data set.

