Given that only a small proportion of the raw video signal is relevant for rPPG measurement of VS (1%-2%), we are developing ways to enhance data collection and signal processing. Video recordings will be of higher resolution than those in the VISION-V and VISION-D studies, and data processing is focusing on the midface region (cheeks, nose, and top of the lip), rather than the whole face; these areas are computationally efficient for rPPG because of their large area and good-quality signal [16] but are not likely to be affected by autoregulation of cerebral blood flow (which discounts the forehead) [17]. We are also developing a method to identify small regions of interest in the midface in each participant where signal quality is the highest. This approach is expected to overcome some of the challenges of rPPG for routine clinical use, such as positioning of the participant relative to the light source.

VISION-MD (Clinicaltrials.gov NCT04763746) aims to advance the development and accuracy of the Lifelight app as a noninvasive and easy-to-use device to measure VS in hospitals and the community. The study will collect data from a broad range of patients to further develop the accuracy of Lifelight to a level sufficient for clinical applications, including screening and monitoring of cardiovascular disease. The initial data collected are being used for machine learning; later data will be used to test the accuracy of Lifelight compared with standard-of-care measurement of VS.

Thus, the primary objective of VISION-MD is to further develop the Lifelight algorithms across extensive clinical ranges, including critically ill patients and in patients with different skin tones. Secondary objectives are: (1) to improve and test the efficacy of Lifelight estimates for BP, pulse rate, respiratory rate, and oxygen saturation in multiple clinical settings (eg, critical care, outpatient clinics, and general hospital wards); (2) to evaluate the impact of variables on the accuracy of Lifelight VS measurements (eg, age, sex, temperature, health condition, medication, skin tone, and ambient lighting); (3) to understand the health economic potential of Lifelight; and (4) to compare the patients’ experience of current contact-based methods for measuring VS and Lifelight and to evaluate the patients’ acceptance and appetite for Lifelight.

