### Performance Targets

The accuracy of Lifelight using the training data generated in VISION-D was sufficient to support the certification of Lifelight as a class I CE medical device [15]. However, the accuracy needs to be improved further for use in routine clinical practice. Table 2 lists the performance targets for Lifelight; training data collected during VISION-MD will support the progress toward these targets.

**Table 2 table2:** Performance (accuracy) targets for Lifelight.

Vital signs	Accuracy target	Basis for target
Blood pressure	SBP^a^ can be measured with standard deviation ≤8 mm Hg British Hypertension Society Grade C for SBP measurement	ISO81060-2^b^ for blood pressure cuffs [19]
Pulse rate	Root mean square error of ≤3 beats per minute	Most common accuracy of CE^c^-marked commercially available devices
Respiratory rate	Maximum error tolerance of 5 breaths per minute	Accuracy of Philips Health watch, a CE-marked contact-based photoplethysmography device
Oxygen saturation	Maximum error tolerance of 4%	ISO80601-2-61 standard for pulse oximeters [20]

^a^SBP: systolic blood pressure.

^b^ISO: International Organization for Standardization.

^c^CE: Conformité Européenne.

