### Sample Size

The sample size cannot be formally calculated because it depends on the incremental improvement in the accuracy of Lifelight achieved through machine learning using the training data generated in the study. However, indicative sample sizes for the 4 subprotocols have been calculated by assessing the optimal data requirements to enable algorithm training toward the standards defined in Table 3, balanced against the practicality of achieving the targets. The split between training and testing data will be determined during the study according to the quality of the data collected.

The initial protocol anticipated data collection from about 8400 participants for training and a further 1000 for independent testing of accuracy, but the recruitment has been compromised by restrictions implemented during the COVID-19 pandemic. However, the high-quality video recording (compared with VISION-D and VISION-V) supported a protocol amendment to reduce the recruitment to 1950 participants (see Results section), with the expectation that data from about 1700 will be used for training the algorithms and data from 250 used for testing. The study management team is monitoring the progress of data collection and accuracy, and updates the study teams monthly. The study will continue until the accuracy of Lifelight for measuring VS is sufficient for various clinical use cases.

As skin tone is expected to affect the accuracy of Lifelight, the aim is to recruit participants across the full Fitzpatrick skin tone scale (1-6). To allow the impact of skin tone measurement accuracy to be determined with statistical robustness, the full data set will be sampled to create a subset for skin tone analyses in which the prevalence of the usually less prevalent skin tones is amplified. This subset will contain 750-1000 measurements, with 15%-20% each from categories 1, 2 and 3, 4, and 5 and 6. These measurements should be spread across the subprotocols as indicated in Table 3.

**Table 3 table3:** Indicative sample size targets.

Subprotocol	Indicative sample size, n^a^	Characteristics	Participants with skin tone categories 1, 4, 5, and 6
1	1500	Roughly 100 participants will be recruited with SOC^b^-determined SBP^c^ in each 10 mm Hg increment from <90 mm Hg to >200 mm Hg (ie, <90 mm Hg; 90-99 mm Hg; 100-109 mm Hg, etc)^d^	Ideally ≥4 in each SBP band
2	375	N/A^e^	Ideally ≥10 in each SBP band

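### The Table 2 accuracy targets carry no skin-tone condition, and the only planned skin-tone analysis draws mostly on training data, so the plan gives no held-out check of the targets by skin tone

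*Protocol article*

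**What the plan says.** - **Objective (Protocol article, Introduction).** The primary objective is to "further develop the Lifelight algorithms across extensive clinical ranges, including critically ill patients and in patients with different skin tones". A secondary objective is to evaluate how several variables, skin tone among them, affect accuracy.
- **Targets (Performance Targets, Table 2).** There is one entry per vital sign. For SBP it reads "SBP^a^ can be measured with standard deviation ≤8 mm Hg British Hypertension Society Grade C for SBP measurement". No entry refers to skin tone.
- **Use of the targets (Data Analysis).** "The test data will subsequently be used to determine the performance of Lifelight against the targets set out in Table 2". No strata are mentioned.
- **Expected effect (Sample Size).** "As skin tone is expected to affect the accuracy of Lifelight, the aim is to recruit participants across the full Fitzpatrick skin tone scale (1-6".
- **Skin-tone analysis (Sample Size).** "the full data set will be sampled to create a subset for skin tone analyses". It is to hold 750-1000 measurements, with 15%-20% from each of four groups: category 1; 2 and 3; 4; 5 and 6. No accuracy limit is attached.
- **Train/test division (Sample Size).** 1950 participants are planned, "with the expectation that data from about 1700 will be used for training the algorithms and data from 250 used for testing". However, "The split between training and testing data will be determined during the study according to the quality of the data collected".

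**The concern.** The plan expects accuracy to depend on skin tone, yet neither of its two analyses tests the targets by skin tone in participants the algorithm has not seen.

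- The comparison with Table 2 uses held-out data but has no skin-tone breakdown.
- The skin-tone analysis has the breakdown, but its data come from the whole study, most of which trains the algorithm. Error on training data tends to be smaller than error on new data.

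Table 3 makes the rarer tones a small minority within each SBP band, so an overall SD is driven by the other tones. The study could report the SBP target as met and leave open whether it holds in the tones where accuracy is most in doubt.

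**Working it through.** **1. The plan's own figures.** 1700 + 250 = 1950, as stated. The article gives no error SD by skin tone, so there is no such figure to reproduce.

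**2. How much of the skin-tone subset can be held-out data?**
- Expected training share of participants: 1700/1950 = 87%.
- Each skin-tone group in the subset needs between 0.15 × 750 ≈ 113 and 0.20 × 1000 = 200 measurements.
- If types 5 and 6 are 8% of the 250 test participants, that is 20 people. At three recordings each (the Table 1 maximum per session), one session each yields 60 measurements, below 113.
- So unless test participants contribute many repeat sessions or the test set is enriched, the subset must rely on training data.

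**3. Share of the less common tones.** Table 3 asks ideally for at least 4 participants per SBP band from categories 1, 4, 5 and 6, out of roughly 100. Read as 4 in total, this is 4%. Read as 4 per category, it is 16% for all four and 8% for types 5 and 6 alone. These are floors, not forecasts.

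**4. Overall SD as a mixture.** Assume equal mean errors. With share *p* at SD 12 (1.5 × 8, an assumed value) and the rest at SD *s*:

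overall SD = √[*p* × 144 + (1 − *p*) × *s*²]

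- *p* = 0.08, *s* = 7.0: √(11.52 + 45.08) = 7.52
- *p* = 0.08, *s* = 7.5: √(11.52 + 51.75) = 7.95
- *p* = 0.16, *s* = 7.0: √(23.04 + 41.16) = 8.01
- *p* = 0.16, *s* = 7.5: √(23.04 + 47.25) = 8.38

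Setting the overall SD to 8 gives the largest *s* that still meets the limit: 7.79 at a 4% share and 6.98 at 16%. If *p* exceeds 64/144 = 44.4%, the true overall SD exceeds 8 whatever the other tones do.

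**5. How often the sample SD is ≤8.** Assumed SBP test set: 250 × 1500/1950 ≈ 192 participants, one reading each, normal errors. Simulated:

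| Share at SD 12 | Rest SD 7.0 | Rest SD 7.5 |
|---|---|---|
| 4% | 97% | 75% |
| 8% | 88% | 57% |
| 10% | 80% | 47% |
| 16% | 50% | 21% |

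With the rest at SD 6.5 and a 16% share, the figure is 78%.

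**6. What a breakdown could show.** By the chi-square distribution of a sample variance, a group with true SD 12 shows a sample SD ≤8 about 4% of the time with 15 participants (8% of 192) and 0.4% with 31 (16%). But a group with true SD 7.5 and 15 participants exceeds 8 about 32% of the time. An observed SD of 8 from 15 participants has a 95% interval of about 5.9 to 12.6.

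**The case against.** **The article is silent rather than wrong.** It never says that the targets are assessed once, or on pooled data. It condenses a fuller protocol, and the SAP is not shown, so a skin-tone criterion may exist there. This stands: a single pooled assessment is the natural reading, not a stated rule. The source of the skin-tone subset, however, is stated, and it is the full data set.

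**The primary objective is development.** A reader might infer that the study's primary aim is to show accuracy in every skin tone, so that a pass mark per tone is owed. The text does not support this. The primary objective is to develop the algorithms; skin tone's effect on accuracy is a secondary estimation question, which needs no pass mark.

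**Skin tone is not ignored.** Recruitment can be steered by skin tone, and an enriched subset is planned. A large difference could show up there. This also stands, with the limit that error in that subset may look smaller than in new participants.

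**The illustration is chosen.** A reader might infer that Lifelight will pass with an error 1.5 times the limit in the less common tones. The documents give neither that ratio, nor the SDs, nor the tone mix of the test set. If all four less common categories make up 16%, the target is missed about half the time or more when the rest have SD 7.0 or above. The masking is shown only for the SBP SD. The respiratory rate and oxygen saturation targets are maximum errors, which pooling does not dilute if taken literally. The SBP target also names Grade C, whose cut-offs the article does not give.

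**Conclusion.** The concern holds in a limited form. As written, the targets have no skin-tone condition, and the one skin-tone analysis is not confined to held-out data. Following the article would therefore not show whether the Table 2 targets hold by skin tone in unseen participants, although the plan expects skin tone to matter.

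The size for SBP depends on assumptions. With a true SD of 12 in the less common tones and 7.0 to 7.5 in the rest, the overall target is met in 57% to 88% of test sets at an 8% share and 21% to 50% at 16%. These figures assume 192 participants, one reading each, normal errors and equal mean error across tones. They show that masking is possible at the shares Table 3 suggests, not that it is likely, and it cannot arise above a 44% share. Because the split is decided during the study, the share in the test set is unknown.

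**What to change.** In Data Analysis, add that each Table 2 statistic is also reported in the held-out test data by the protocol's own skin-tone groups (1; 2 and 3; 4; 5 and 6), with confidence intervals. Add that an overall 'target met' result is not extended to a group whose interval is too wide to assess; that group is reported as 'not established'.

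Do not apply a pass/fail gate to the point estimate in small groups. With about 15 participants it would fail a compliant group (SD 7.5) roughly a third of the time.

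The cost is a few extra rows of analysis on data already collected. The drawback is wide intervals in the rarer groups and possibly a narrower claim.

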The VISION-D (Measurement of Vital Signs by Lifelight Software in Comparison to the Standard of Care-Development) study measured VS in 8585 patients and healthy volunteers simultaneously using Lifelight and standard-of-care methods. The data were used for machine learning to improve the accuracy of the Lifelight algorithms used to calculate VS. The smaller VISION-V (Measurement of Vital Signs by Lifelight Software in Comparison to the Standard of Care–Validation) study demonstrated the accuracy of the Lifelight app compared with standard-of-care methods for measuring pulse rate, respiratory rate, and diastolic BP [14], providing the basis for the current class I Conformité Européenne (CE) registration [15]. However, some of the methods used in the VISION-V study differed from the procedures described in the standard for BP measurement (ISO81060-2) because of the novel nature of the Lifelight technology. Furthermore, these early studies did not include participants with BP values across the full range likely to be encountered in clinical practice.

To further improve the accuracy of Lifelight, the Measurement of Vital Signs by Lifelight Software in Comparison to the Standard of Care–Multisite Development (VISION-MD) study is collecting data from a wide range of outpatients, inpatients, and patients who are critically ill, and across the full range of skin tones, for use in machine learning. In VISION-D and VISION-V, full-face videos were recorded, but a high proportion of data were not usable. Thus, high-resolution full-face videos are being recorded to maximize the opportunity for machine learning. These data will also be used to evaluate alternative methods of defining the region of interest, as the full face includes areas that are not relevant (eg, areas covered by facial hair and areas that illicit a poor signal).

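### The test-set exclusion rule does not separate reference faults from device failures, so Table 2 results would describe accuracy only where Lifelight gave an acceptable reading

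*Protocol article*

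**What the plan says.** All references are to the protocol article.

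- **Data Analysis, purpose of the test data:** "The test data will subsequently be used to determine the performance of Lifelight against the targets set out in Table 2".
- **Data Analysis, exclusions:** there is no imputation, and "any missing, implausible, or problematic readings will be excluded from the analysis". The article does not define implausible or problematic, does not say whether the reading meant is the reference or the Lifelight value, and does not say who decides or with what information.
- **Data Analysis, face not detected:** "this will be recorded in the electronic case report form, and the measurements will be deleted from the data set".
- **Data Analysis, analysis set:** "All analyses will be completed per protocol since there is no intention to treat".
- **Performance Targets, Table 2:** systolic pressure "can be measured with standard deviation ≤8 mm Hg"; for pulse rate, "Root mean square error of ≤3 beats per minute"; maximum errors of 5 breaths per minute for respiratory rate and 4% for oxygen saturation. No target concerns the proportion of attempts that yield a reading.
- **Introduction, on the two earlier studies:** "full-face videos were recorded, but a high proportion of data were not usable".

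**The concern.** Discarding poor recordings can be reasonable when training an algorithm. In a performance test it changes the quantity being estimated. If a cuff reading is faulty, the pair says nothing about Lifelight and should go. If Lifelight gives an absurd value, or cannot find the face, that is itself information about performance. One rule covers both cases, and it applies to training and test data alike.

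Two things are at stake. First, all four Table 2 criteria are sensitive to extreme errors, so removing even a few bad device outputs can turn a fail into a pass. Second, secondary objective 2 asks how skin tone, ambient lighting, health condition and other variables affect accuracy, and the Sample Size section expects skin tone to matter. If failures are more common in some groups, an analysis of successful readings alone could show similar accuracy across groups while the device fails more often in one of them. Such clustering is plausible, but the article gives no figure for it.

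**Working it through.** **Inputs from the document.** Targets: SBP SD 8 mm Hg, pulse RMSE 3 beats per minute, and the two maximum errors (Table 2). Test set: 250 participants (Sample Size). The only related figure that can be reproduced is the recruitment total, 1700 + 250 = 1950, which agrees. The document gives no exclusion rate, failure rate or error distribution, so the fractions below are assumptions.

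**1. Largest possible effect on an SD for a given share removed, normal errors.** If the fraction f with the largest absolute errors is removed from a centred normal distribution, the remaining SD is the true SD times

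r = sqrt(1 − 2·c·φ(c)/(1 − f)), with c the standard normal quantile at 1 − f/2.

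The true SBP SD that shows as 8.0 is 8/r. The true pulse RMSE that shows as 3.0 is 3/r.

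| f | c | r | 8/r (mm Hg) | 3/r (beats/min) |
|---|---|---|---|---|
| 2% | 2.33 | 0.935 | 8.56 | 3.21 |
| 5% | 1.96 | 0.871 | 9.18 | 3.44 |
| 10% | 1.645 | 0.789 | 10.14 | 3.80 |

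With heavier tails (t distribution, 4 degrees of freedom, numerical integration), r is 0.837, 0.750 and 0.657, and the SBP figures become 9.56, 10.67 and 12.19. The bound is therefore specific to normal errors.

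**2. A few gross failures.** Suppose 95% of readings have error SD 7 and 5% are gross failures with SD 25. Overall SD = sqrt(0.95 × 49 + 0.05 × 625) = sqrt(77.8) = 8.8, which misses the target. If exactly the failures are dropped, the SD is 7.0, which meets it.

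**3. Maximum-error targets.** Read as a limit on every reading, and assuming 250 independent test readings: if 1% of readings exceed the tolerance, the chance that none does is 0.99^250 = 0.08, with 2.5 expected. At 0.5% it is 0.995^250 = 0.29, with 1.25 expected. Excluding one to three readings could settle the result.

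**4. Failures left out of the denominator.** If 95% of analysed readings are within tolerance, the share of attempts giving an acceptable result is 0.95 × (1 − failure rate):

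- 5% failures: 0.90
- 10%: 0.86
- 20%: 0.76
- 30%: 0.67

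Two skin tone groups with failure rates of 5% and 20% would look identical among analysed readings (95% each), but would differ as 90% against 76% of attempts.

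**The case against.** The strongest reply has four parts.

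- **Implausible describes a value, not a disagreement with the cuff.** The cut-offs implied by step 1 are errors of about 20 mm Hg (2.33 × 8.56), 18 mm Hg (1.96 × 9.18) and 17 mm Hg (1.645 × 10.14). The study seeks systolic pressures from below 90 to above 200 mm Hg (Table 3), so an estimate wrong by that much would often still be a plausible pressure and be kept. This stands: the step 1 figures are a bound, not a model of the stated rule.
- **The rule may be meant for reference readings.** The app returns no measurements to the user or participant (VS measurement), so at the session staff see only standard-of-care values and recording problems. The terms may also be defined in the full protocol or SAP. This stands in part. A reader might infer that the plan sets out to trim Lifelight's largest errors, but the article states no such intention. Its wording nevertheless permits it, and nothing requires blinding to the Lifelight value.
- **Failures are not lost.** A reader might infer that deletion destroys the evidence of failure. It does not: the same sentence has the event logged in the electronic case report form, and VS measurement lists it among the postmeasurement observations. What the article leaves out is its place in the performance assessment.
- **This is a development study.** The data collection app is not shown to have the finished product's failure rate, and no section says the results will be presented as unconditional accuracy in routine use. The remark on unusable data concerns the earlier studies and motivates the higher-resolution video. It supplies no rate for this study. All of this is fair. Even so, the test set is what decides whether the targets are met, and the stated aim is use in hospitals and the community.

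Face-not-found is also a separate matter from trimming. With no face detected there is no error to enter an SD, so only step 4 applies to it.

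**Conclusion.** The point holds as a defect in a stated rule, not as a missing detail. Followed as written, it yields accuracy conditional on an acceptable reading, with device failures outside the assessment and no safeguard on how exclusions are decided.

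The direction of any bias from dropping implausible or problematic Lifelight outputs is optimistic. Its size is not derivable. The figures of 8.6, 9.2 and 10.1 mm Hg assume normal errors, removal of exactly the largest paired differences, and removal fractions of 2%, 5% and 10% that the document does not give. If only reference readings are ever excluded, without sight of the Lifelight value, this part of the concern largely falls away and the face-not-found part remains. Differential failure by skin tone, lighting or illness is something the analysis could hide, not something the article shows to exist.

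**What to change.** For the test data, replace the exclusion wording with three rules:

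1. Exclude a pair only for a fault in the reference measurement or in the recording procedure, decided without sight of the Lifelight value.
2. Keep every Lifelight output, including implausible ones, unless an automated rule fixed before the test data are analysed rejects it.
3. Flag face-not-found and rejected recordings instead of deleting them. Report the failure proportion beside each Table 2 result, overall and by skin tone, setting, lighting and movement.

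The cost is analysis wording. Face-not-found, movement and background light are already recorded (VS measurement), skin tone is used in recruitment (Subprotocol assignment), and clinical setting is already part of secondary objective 1. Training data can be filtered as the developers see fit. The downside is that reported accuracy may be somewhat less favourable. The change should be made before the test data are analysed.
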